### Interventions

We will use a pragmatic approach in this trial. That is, the interventions are meant to reflect exercise delivery options that could realistically be implemented in clinics and the community. The primary advantage of this approach is that its results are more likely to translate to the ‘real-world’. Both interventions are designed to help participants reach exercise recommendations for the prevention and therapy of dementia (≥150 min/week of moderate aerobic exercise with resistance training 2×/week) by the end of the intervention period. [11] The exercise prescriptions for participants in both groups will be individualized in consideration of the participant’s baseline exercise, fitness, and mobility and will progress gradually to meet targets.

#### Centre-based exercise

A certified exercise physiologist will lead 60 min exercise sessions that include both aerobic, resistance, balance, and flexibility training at the centre once per week in a small group setting (3 to 5 participants), which is a frequency and duration often available in clinical and community exercise programs. Treadmill or Nustep will be the main aerobic training modalities during in-class sessions. Intensity will be monitored by heart rate and rating of perceived exertion (RPE, target: 12–15/20). Resistance training will target major muscle groups using exercise machines and hand-held weights as well as through functional activities. Exercise classes at the centre will be complemented by additional exercise to be performed independently at-home or in the community. The exercise physiologist will prescribe at-home exercise and collaborate with the participant to develop a plan for meeting the prescription. Participants will be encouraged to invite their care partner to attend this session. Participants will use an exercise diary to record their daily exercise.

#### Home-based exercise

The HB program replicates an intervention used previously among middle to older aged adults, [28] except that care partners will be involved in the program planning. As with the at-home portion of the CB group, the exercise physiologist will prescribe exercises to be performed independently at-home or in the community and will develop a plan with the participant and care partner for meeting the prescription. The participant will mail in their exercise diary monthly. In addition, the exercise physiologist will talk to the participant and care partner each month by phone to discuss achievements and strategies to overcome recent barriers. Following the call, the exercise physiologist will adjust the exercise prescription and mail it to the participant with instructions to contact if there are any questions.

### Measures

All participants will be assessed at the center at baseline and after the intervention. Participants will also complete a telephone assessment 1 month and 2 months into the program. Measures by time points are listed in Table 1. Assessors are blinded to group allocation throughout the study. Any possible disclosure will be noted.

**Table 1 Tab1:** Assessments by time point

	Baseline	1-month	2-month	Post-intervention
Participant Descriptors				
Participant information questionnaire	X			X
Height, weight, waist, BP	X			X
Medications	X			X
Physical activity history	X			
Social Support for exercise survey	X			X
BBAQ	X			X
Self-reported health	X	X	X	X
Falls	X	X	X	X
Secondary & Tertiary Outcomes				
RUD-Lite	X	X	X	X
PASE	X	X	X	X
ADAS-Cog	X			X
Stroop Test	X			X
Trails Making Task	X			X
Semantic Fluency	X			X
SPPB	X			X
DAD-6	X			X
EQ-5D	X			X
NPI-Q	X			X
6 min walk	X			X
25 ft. single & dual task	X			X
GAS	X			X
Primary Outcome				
Actigraph	1-week following			1-week following

*BP* blood pressure, *BBAQ* Barriers to Being Active Questionnaire, *RUD-Lite* Resource Utilization Dementia-Lite questionnaire, *PASE* Physical Activity Scale for the Elderly, *ADAS-Cog* Alzheimer Disease Assessment Scale-cognitive, *SPPB* Short Physical Performance Battery, *DAD-6* 6-item Disability Assessment for Dementia scale, *EQ-5D* Euro-Qol 5D, *NPI-Q* Neuropsychological Inventory, *GAS* Goal Attainment Scaling

#### Primary outcome

The primary outcome will be achievement of aerobic activity guidelines for older adults (percent of 150 min/week of moderate physical activity) as measured using an activity monitor (Actigraph GTX3+), [29] which contains an accelerometer that is validated for measurement of physical activity by intensity among older adults. [30, 31]. Participants will wear the activity monitor for one week following the baseline assessment, with the expectation that at least 5 days of usable data will be achieved as is required for reliable estimates of habitual physical activity. [32] Wear time will be validated by established parameters. [33] We will determine time spent in moderate or vigorous physical activity using cut-offs based on recent studies of older adults (≥810 cpm). [35] The time spent in moderate or vigorous activity will be divided by the recommendation (150 min/week or 21.4 min/day) to get percent achievement of the guidelines.

#### Secondary and tertiary outcomes

*Cost-effectiveness* will be determined by cost per unit change in physical activity (min/wk. of moderate physical activity). Participants will report health-care utilization each month, including visits to health care professionals, admissions or visits to the hospital, and laboratory work using the Resource Utilization Dementia (RUD)-Lite questionnaire, as employed in previous studies regarding exercise in cognitively impaired populations. [34, 35] Costs will then be assigned to health-resource utilization data (using a Canadian healthcare system perspective) and combined with the costs for each intervention group to generate a cost per min/week of exercise.

*Physical Activity* will also be reported at baseline, monthly during the intervention, and post-intervention using the Physical Activity Scale for the Elderly (PASE). The PASE is valid among older adults aged 65–100 years and for proxy responses by care partners. The PASE will be used to track physical activity change by month over the course of the intervention, to better understand the change in physical activity over time. In addition, it will be used to assess achievement of resistance training guidelines (2×/wk). [36]

*Cognitive Function* will be assessed with three measures. The Alzheimer Disease Assessment Scale-cognitive (ADAS-Cog) will be used to assess global cognitive function. [37] The ADAS-Cog is considered sensitive to the earliest cognitive changes in MCI and has been sensitive to exercise interventions. [24, 38] The Stroop Test will be used to measure executive function (inhibition), [39] which is arguably the cognitive domain most sensitive to exercise effects. [40] The Trail Making Task and Semantic Fluency will additionally be used to test additional components of executive function and language. [41, 42]

*Physical function* will be assessed using a 6-min walk test, the Short Physical Performance Battery, and single and dual-task gait. [43, 44] The 6-min walk is a functional measure of aerobic fitness that has a reliability of 0.95 among older adults. [44] The Short Physical Performance Battery includes measures of functional strength (chair stands), balance (semi-tandem, side-by-side, tandem stand), and walking speed (4 m walk) and is associated with functional disability, mortality, and institutionalization among older adults. [43] Gait speed will also be measured over 25 ft. Participants will complete a single task gait speed assessment, where they will walk the 25 ft. course at their usual walking speed. Participants will also complete a dual task gait speed assessment where they will walk the 25 ft. course at their usual walking speed, while simultaneously reciting words aloud that begin with a specified letter of the alphabet.

*Daily function* will be assessed with the 6-item Disability Assessment for Dementia scale (DAD-6), [45] .which is intended to detect early changes in activities of daily life in people with cognitive impairment. [45]

*Apathy and depressive symptoms* will be assessed using the Neuropsychological Inventory, which is a valid and reliable tool for the assessment of neuropsychiatric symptoms in people with cognitive impairment. [46]

*Health-Related Quality of Life* will be measured using the EuroQol 5D (version EQ-5D-3 L), [47] which had the best convergent validity among self- and proxy-ratings for people with cognitive impairment. [48] The EuroQol 5D can also generate utility measurements for different health states, which can be employed for cost-utility analyses.

*Physical Health* will be characterized using height, weight, waist circumference, and blood pressure. We will use this data to create simple indicators of vascular risk (hypertension, obesity).

*Goal attainment* of individually-important goals will be measured using goal attainment scaling. [49, 50] Goal attainment scaling is a feasible, valid, and reliable method of goal setting and measurement in older adults. [49, 50] At least three individually-important goals will identified by the participant. The expected outcome (score of 0) will be no change from the current state. Criteria for better or much better than expected and for less than and much less than expected will then be determined jointly between the individual and the exercise physiologist. At the post-intervention assessment, each attainment of each goal will be scored between −2 and +2.

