Trials of exercise interventions among people with MCI or dementia indicate that both CB and HB exercise can be effective for improving cognitive, physical, and other outcomes (for example, [23, 26]). It is possible that the most effective option will not be uniform even within this clinical group but may depend further on the individual (e.g., degree of care partner support, diagnosis (i.e. MCI vs dementia), severity of deficits) and the context (e.g., weather, proximity to facilities). Consequently, the aim of this study is to compare the effectiveness of CB versus HB exercise programs in achieving aerobic exercise guidelines (percent of 150 min per week of moderate intensity activity) among people with MCI and mild dementia. Secondary objectives will compare the cost-effectiveness of the interventions and examine the influence of individual and environmental factors on achievement of the primary outcome. Exploratory objectives will compare the effect of CB and HB exercise on physical function, cognitive function, vascular health, quality of life, instrumental activities of daily living (IADLs), mood, and individual goal attainment. Based on prior results among healthy older adults, [27] we hypothesize that participants assigned to the HB exercise group will have a higher percent achievement of physical activity guidelines compared to the CB exercise group. Conversely, we hypothesize that the CB group will experience greater gains in physical function than the HB group.

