### Sample size calculation

Sample size is based on the primary objective, to detect a significant difference in percent achievement of physical activity recommendations (continuous variable) between CB and HB groups over the intervention period. A recent Cochrane review of CB versus HB among older adults indicated that HB exercise had better physical activity achievement than CB, with an effect size of 0.8. [27] There were no studies that targeted people with cognitive impairment. To account for the possibility that cognitive impairment may reduce the feasibility of HB, we used a smaller effect size of 0.6, an alpha of 0.05 and a beta of 0.85 with two-group repeated measures MANOVA (within and between factors) to estimate a sample size of 39. We assumed 35% drop out, similar to our pilot work and to a previous study of exercise in people with MCI, [54] to bring the required sample size to 60.

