#### Tertiary objective

Change in each tertiary outcomes between T1 and T2 will be examined using mixed effects linear regression as a function of group, time, and group x time interaction. A random effect for participants and site will be included in the models.

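### Vascular health is to be compared between arms, but the only derived variables are hypertension and obesity indicators, which use less information than the continuous measures already taken at both visits

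*Protocol article*

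**What the plan says.** Four parts of the protocol article bear on this.

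- **Objective (Background).** "Exploratory objectives will compare the effect of CB and HB exercise on physical function, cognitive function, vascular health", followed by several further outcomes. Vascular health is therefore a comparison between arms.
- **Definition (Secondary and tertiary outcomes, Physical Health paragraph).** Physical health "will be characterized using height, weight, waist circumference, and blood pressure". The next sentence reads: "We will use this data to create simple indicators of vascular risk (hypertension, obesity"). No continuous vascular endpoint is named.
- **Timing and role (Measures, Table 1).** The row "Height, weight, waist, BP" is marked at baseline and post-intervention. It stands in the Participant Descriptors block, not in the block for secondary and tertiary outcomes. The Individual characteristics section lists the measures again.
- **Analysis (Tertiary objective).** The model is given in one sentence: "Change in each tertiary outcomes between T1 and T2 will be examined using mixed effects linear regression". Its terms are group, time and their interaction, with random effects for participant and site. No exception is made for categorical outcomes.

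**The concern.** Blood pressure, waist and weight are recorded on continuous scales at both visits, so every completer has a measured change. Taken together, the sections point to a comparison of hypertension and obesity status. A participant who improves without crossing a cut-off then counts as unchanged, and one who sits near the cut-off can switch on a trivial difference.

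At stake is the precision of one exploratory comparison in a trial that plans for about 39 completers. The inconsistent filing adds to this: a reader cannot tell whether these measures are outcomes to be compared or only a description of the sample.

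**Working it through.** **Inputs from the article.** Sample size calculation: 39 analysable participants and 35% dropout. The article's 60 follows: 39 / (1 − 0.35) = 60. It gives no figure for the vascular outcome, so there is none to reproduce; 39 serves below as the number of completers.

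**Inputs assumed.** The article gives no prevalence, no baseline-to-post correlation and no expected vascular effect. Prevalence p is varied from 20% to 50% and correlation r from 0.6 to 0.95. Effects of 0.3 and 0.6 SD are illustrative. The 0.6 is the size of the figure in "we used a smaller effect size of 0.6, an alpha of 0.05 and a beta of 0.85", but that figure concerns physical activity and its metric is not named.

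**Step 1: single visit.** For a normal measure cut at prevalence p, with c the cut-off in SD units and φ the normal density, the relative efficiency is φ(c)² / [p(1 − p)].

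| p | φ(c) | Efficiency | × 39 |
|---|---|---|---|
| 50% | 0.3989 | 0.1592 / 0.25 = 0.637 | 24.8 |
| 30% | 0.3477 | 0.1209 / 0.21 = 0.576 | 22.5 |
| 20% | 0.2800 | 0.0784 / 0.16 = 0.490 | 19.1 |

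A 50% prevalence is the most favourable case for the indicator.

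**Step 2: change between visits.** The tertiary model concerns change, so Step 1 alone is not the right quantity. Continuous change has variance 2(1 − r) in SD units. Change in a 0/1 indicator has variance S, the probability of switching category, when there is no overall shift. A small effect δ moves the indicator mean by φ(c)δ. The relative efficiency for change is therefore φ(c)² × 2(1 − r) / S.

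At p = 50%, S = arccos(r)/π:

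- r = 0: S = 0.500; 0.1592 × 2.0 / 0.500 = 0.637, which is the single-visit value.
- r = 0.7: S = 0.253; 0.1592 × 0.6 / 0.253 = 0.38.
- r = 0.9: S = 0.144; 0.1592 × 0.2 / 0.144 = 0.22.

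The loss for change thus exceeds the single-visit loss at these positive correlations, and it grows as r rises.

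**Step 3: check by simulation.** Groups of 20 and 19, 20,000 runs, two-sided 5% t test on change. With two visits and complete data this matches the group-by-time test. Each range covers prevalences of 30% and 50%.

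| r | Effect | Power, continuous | Power, indicator | Switchers of 39 |
|---|---|---|---|---|
| 0.7 | 0.6 SD | 0.65–0.66 | 0.19–0.27 | 8.5–9.9 |
| 0.7 | 0.3 SD | 0.22 | 0.09–0.10 | 8.6–9.9 |
| 0.9 | 0.6 SD | 0.98–0.99 | 0.27–0.38 | 4.8–5.6 |
| 0.9 | 0.3 SD | 0.52–0.54 | 0.12–0.14 | 4.9–5.6 |

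Over r from 0.6 to 0.95, the number of switchers runs from about 11.5 down to about 3.4.

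**The case against.** The strongest reply is that the article does not state this plan in one place. It does not call the indicators binary, and it does not say that they replace the measures. The sentence before them characterises physical health by the measures themselves. Table 1 and the Individual characteristics section treat the measures as descriptors, and the Abstract's tertiary outcomes include nothing vascular. On that filing the tertiary model never reaches them. Hypertension status might also draw on recorded medications or conditions and so not be a pure blood-pressure cut. Definitions and cut-offs may stand in a fuller document.

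Much of this stands, and it limits the claim. The article does not establish that the measures are reduced to yes/no variables; that is an inference, though hypertension and obesity are ordinarily threshold conditions. Missing cut-offs are no fault in a condensed article. The descriptor filing does not remove the point, however, because the Background promises a comparison of arms and the Physical Health paragraph sits under the outcomes heading. The conflict is a reason to say what is compared.

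A reader might also infer that a linear model of a 0/1 outcome is invalid. That goes too far: its coefficients can be read as risk differences. The information loss does not depend on that choice.

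**Conclusion.** The point holds as a minor one. Vascular health is a declared comparison, the only derived vascular variables are indicators most naturally read as threshold-based, and continuous values exist at both visits. If arms are compared on those indicators, about 36% to 51% of the information is lost at a single visit (prevalences 50% to 20%), and more for change.

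The direction of the loss rests on the threshold reading; its size rests on assumed normality, prevalence, correlation and effect, none of which the article gives. A reader might conclude that the comparison is close to uninformative, or that some fixed small number of participants decides it. The document supports neither: the number who switch category varies about threefold over the correlations tried, and reporting of the continuous values is not excluded. Nothing is lost irrecoverably, because the measurements are taken in any case. The primary conclusion and the sample size are untouched.

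**What to change.** State that the arms are compared on systolic blood pressure, diastolic blood pressure, waist circumference and weight as continuous outcomes. Either of two models will do:

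- the Tertiary objective model as it stands (group, time and their interaction). Baseline is already one of the responses, so no baseline covariate should be added, since that would use baseline twice;
- a model of the post-intervention value adjusted for its baseline value.

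Keep the hypertension and obesity indicators for description and as baseline characteristics. Show the measures in Table 1 as exploratory outcomes as well as descriptors, so that it agrees with the Background.

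The cost is a sentence or two and no new data. The downside is a few more exploratory outcomes in an already long list; they should be reported as exploratory, without multiplicity control.

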#### Individual characteristics

Participants will report demographic information, education, medications, and co-morbid conditions at baseline. Each participant will have height, weight, waist circumference, and blood pressure measured. In addition, participants will provide self-reported health (poor to excellent) at baseline, monthly, and post-intervention. Participants will also report their history of injury, surgery, and major diseases as well as current health conditions and medications. Use of a mobility aid and recent falls will be reported.

Exercise in the teenage years and mid-life will be reported as history of participation in strenuous exercise 3×/week (Y/N as done previously). [51] Barriers to exercise will be reported using the Barriers to Being Active Quiz, [52] where individuals report how likely they are to say specific statements regarding barriers to exercise. The barriers to exercise are then summarized into six categories: time, social influence, lack of energy, lack of willpower, fear of injury, lack of skill, and lack of resources.

Care partner support for exercise will be gathered using a social support for exercise survey, [53] adapted specifically for care partners.

#### Environmental characteristics

Address will be recorded in order to determine the walkability of the neighborhood, as characterized by Walk Score (www.walkscore.com). The Walk Score is an indicator of sidewalks and neighborhood amenities. Weather, including precipitation and high temperature, will be recorded from Weather Canada reports.

### Sample size calculation

Sample size is based on the primary objective, to detect a significant difference in percent achievement of physical activity recommendations (continuous variable) between CB and HB groups over the intervention period. A recent Cochrane review of CB versus HB among older adults indicated that HB exercise had better physical activity achievement than CB, with an effect size of 0.8. [27] There were no studies that targeted people with cognitive impairment. To account for the possibility that cognitive impairment may reduce the feasibility of HB, we used a smaller effect size of 0.6, an alpha of 0.05 and a beta of 0.85 with two-group repeated measures MANOVA (within and between factors) to estimate a sample size of 39. We assumed 35% drop out, similar to our pilot work and to a previous study of exercise in people with MCI, [54] to bring the required sample size to 60.

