#### Primary objective

Mixed effects linear regression will be used to analyze differences in the primary outcome (percent achievement of physical activity recommendations) as a function of group (CB, HB), time (baseline, follow-up and interim month 1, month 2 where relevant), and group x time. A random effect for participants and site (CB) will be included in the models.

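### If 0.6 is a standardised mean difference, 39 completers give about 45–56% power at a baseline–follow-up correlation of 0.5, not 85%; the printed beta of 0.85 should read power 0.85

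*Protocol article*

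**What the plan says.** Under Sample size calculation, the article starts from a review of older adults in which "HB exercise had better physical activity achievement than CB, with an effect size of 0.8". To allow for cognitive impairment making home exercise less feasible, the authors took a "smaller effect size of 0.6, an alpha of 0.05 and a beta of 0.85 with two-group repeated measures MANOVA", with within- and between-subject factors, "to estimate a sample size of 39". Dropout of 35% brings the total to 60.

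The primary outcome is percent achievement of 150 min/week of moderate activity by Actigraph. In Table 1 (Measures) the Actigraph row has an entry, "1-week following", under baseline and under post-intervention only. Months 1 and 2 are telephone contacts that carry PASE, RUD-Lite, self-reported health and falls. The primary model in the Analysis section uses "time (baseline, follow-up and interim month 1, month 2 where relevant").

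**The concern.** Two things look wrong. The first is on the face of the text: beta is the type II error rate, so a beta of 0.85 means 15% power.

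The second is whether 39 fits the effect the section describes. A between-group effect of 0.8 lowered to 0.6 as a precaution is most readily a difference in means divided by a standard deviation. A two-group comparison of that size at 85% power normally needs about 100 people, not 39. Either a high baseline–follow-up correlation was assumed, or 0.6 was entered on another scale.

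This calculation is the only justification given for 60 participants. If the power for the described effect is near one half, a non-significant difference between delivery options says little. The article's limitations paragraph warns of type II error but attributes it to variability among participants, not to the sizing.

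**Working it through.** **Inputs from the article.** Effect size 0.6 (scale not given), alpha 0.05, power 0.85 (printed as beta), 39 completers in total, 35% dropout, two Actigraph occasions. **Assumed here:** two-sided test, 1:1 allocation (20 and 19 completers), and a range for the baseline–follow-up correlation ρ.

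**1. Reproducing the plan's figures.** For the group-by-time test in a two-group repeated measures MANOVA with m occasions, take λ = N·f(V)², df1 = m − 1, df2 = N − 2 − (m − 1) + 1.
- m = 4, f(V) = 0.6, N = 39: λ = 39 × 0.36 = 14.04, df = (3, 35), power 0.858. At N = 38 power is 0.846, so 39 is the smallest N that reaches 0.85.
- Dropout: 39 / (1 − 0.35) = 60. This reproduces.

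**2. The same calculation with two occasions.**
- f(V) = 0.6, m = 2: N = 28 suffices, and 39 gives power 0.954.
- f(V) = 0.3, m = 2: N = 102, and 39 gives power 0.446.

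Going from four occasions to two therefore does not lower power at a fixed f(V). What matters is the scale. For two equal groups Cohen's f = d/2, so f = 0.6 is d = 1.2 and d = 0.6 is f = 0.3.

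**3. Power of 39 completers if d = 0.6.** The noncentrality is δ = d* / √(1/20 + 1/19) on 37 df, where d* is:
- follow-up only: d* = 0.6, giving δ = 1.87 against a critical value of 2.03;
- change score: d* = 0.6 / √(2(1 − ρ));
- baseline-adjusted: d* = 0.6 / √(1 − ρ²).

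| ρ | Follow-up only | Change score | Baseline-adjusted |
|---|---|---|---|
| 0.3 | 45% | 34% | 48% |
| 0.5 | 45% | 45% | 56% |
| 0.7 | 45% | 65% | 72% |
| 0.8 | 45% | 82% | 86% |

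85% is reached from ρ of about 0.79 with baseline adjustment, and just above 0.81 with change scores.

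**4. Completers needed for 85% at d = 0.6.** Follow-up only: 51 per group, 102 in total (102 / 0.65 = 157 randomised). Baseline-adjusted: 77 at ρ = 0.5, 53 at ρ = 0.7, 38 at ρ = 0.8.

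**5. Effect that 39 completers detect with 85% power.** Unadjusted: d = 0.99. Baseline-adjusted at ρ = 0.5: 0.99 × √(1 − 0.25) = 0.85. The reduced 0.6 is below both.

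**6. If all 60 were retained (30 per group), d = 0.6.** 63% unadjusted; 75% baseline-adjusted at ρ = 0.5.

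**The case against.** Three stronger readings are tempting, and the document supports none of them.

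*That power is lost because the sizing used four occasions and the outcome has two.* Step 2 shows the opposite: on the f(V) scale, two occasions need 28 and 39 gives 95%. Any shortfall comes from the effect-size scale. Nor does the Analysis section contradict Table 1. It lists months 1 and 2 only where relevant, and PASE is indeed collected monthly.

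*That 39 can only come from a four-occasion calculation.* It cannot be pinned down that way. A two-occasion interaction test with f = 0.3 and ρ of about 0.27 also gives 39 (noncentrality N·f²·m/(1 − ρ)), and baseline adjustment with d = 0.6 and ρ = 0.8 gives 38. The four-occasion match is exact and plausible, but it remains an inference.

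*That 39 completers simply lack 85% power.* This depends on the scale. It is false for f(V) = 0.6, and false for d = 0.6 with ρ of about 0.8 or more. The scale of the 0.8 lies in a cited review that is not available here.

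It is also fair to say that an article may leave scale, number of occasions and correlation to the full protocol. Their absence is not the point made here. The point is that the inputs printed, read as the section's own reasoning suggests, do not give the printed result unless the correlation is high.

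Finally, the beta slip is one of wording, since 39 is reproduced with power 0.85. And nothing in the article says that a null result would be taken as similarity.

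**Conclusion.** The point holds in conditional form. The printed beta is wrong without any assumption. If 0.6 is a standardised mean difference, 39 completers give about 45% to 56% power at ρ = 0.5, and 34% to 72% across ρ from 0.3 to 0.7, depending on the analysis. The stated 85% needs ρ of about 0.8 or higher. If 0.6 was instead entered as f(V) with four occasions, 39 is reproduced exactly. Read as Cohen's f for two groups, though, it stands for d = 1.2, which defeats the section's stated aim of being more cautious than 0.8. On either route the stated power is not supported as written for the effect the section describes.

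This rests on a two-sided 5% test, equal allocation, an outcome measured at baseline and post-intervention, and 0.6 being expressed in units of the outcome's standard deviation.

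**What to change.** Keep 60 participants and make these changes to the sample size section:
- Replace the beta of 0.85 with power 0.85 (beta 0.15).
- Label 0.6 as a standardised mean difference. If another scale was used, say so and give the equivalent standardised mean difference beside the 0.8 it was reduced from.
- Restate the calculation for two Actigraph occasions, with the assumed baseline–follow-up correlation.
- State what 39 completers deliver: about 45% to 56% power for d = 0.6 at correlation 0.5, and 85% power only for d of about 0.85 (baseline-adjusted, correlation 0.5) to 1.0 (unadjusted). If a correlation near 0.8 was assumed and can be supported, say that instead.

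The cost is wording only. No participants, visits or analyses change, but the stated power becomes less favourable.
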